## Assessments

### Psychometric instruments

For details of the instruments including psychometric properties, please see online supplemental file 2. All self-report assessments are applied in the study languages, all interviews are applied with the help of interpreters if indicated.

10.1136/bmjopen-2021-057968.supp2Supplementary data

#### Inclusion and exclusion criteria

Inclusion and exclusion criteria are assessed with the Essen Trauma Inventory for Children and Adolescents,^33^ Clinical Global Impression Scale, severity of illness subscale (CGI-S^34^), the Kiddie-Schedule for Affective Disorders and Schizophrenia for School-Age Children-Present and Lifetime version,^35–37^ the Alcohol Use Disorders Identification Test,^38^ the Columbia-Suicide Severity Rating Scale,^39^ the Test of Nonverbal Intelligence, Fourth Edition,^40^ and the standardised Questionnaire to Assess Endangerment to Others.^39^

#### Primary endpoints

Psychological distress is assessed with the Perceived Stress Scale, 10-item version (PSS-10), a validated self-report questionnaire, that measures the intensity with which individuals appraise their daily life as stressful, unpredictable, uncontrollable and overloaded. Reliability and validity for the Arabic, English and German version have been shown to be sufficient or good.^41–44^ Traumatic symptoms are assessed with the Impact of Event Scale-Revised (IES-R), a validated, self-report questionnaire evaluating traumatic symptoms on the subscales intrusion, avoidance, hyperarousal and on an overall measure of traumatic distress. Reliability and validity for the Arabic, English and German version have been shown to be good.^45–48^

#### Secondary endpoints

We assess trauma-related psychosocial impairment and PTSD criteria according to Diagnostic and Statistical Manual of Mental Disorders, 5th ed. (DSM-5) with the Child and Adolescent Trauma Screen-2,^49^ trauma-related cognitions with the Posttraumatic Cognitions Inventory-child version^50–52^ and frequency and intensity of nightmares with the Disturbing Dream and Nightmare Severity Index.^53 54^ Emotion regulation is assessed with the 18-item version of the Difficulties in Emotion Regulation Scale (DERS-18^55^), general psychopathology with the Strengths and Difficulties Questionnaire,^56 57^ and the Beck Depression Inventory, second edition.^58 59^ Overall severity of illness is assessed with the CGI-S.^34^

#### Additional psychometric assessments

We assess adverse life experiences related to migration with the adapted German version of the self-rated PMLD,^60 61^ and therapy expectations with a self-designed questionnaire comprising three questions that are answered on a 5-point Likert-type scale.

### Ambulatory momentary assessment: electronic diaries

We use smartphone-based electronic (e)-diaries to assess aversive inner tension, emotional intensity, trauma symptoms (intrusions, hypervigilance), cognitive and behavioural avoidance of triggering situations in daily environments, sleep quality, stressfulness, content and number of nightmares, self-efficacy, self-esteem, rumination and somatisation.^62–64^ Filling in the answers takes a few minutes and items are available in all study languages. Rumination about cultural differences, social support and conflicts, discrimination experiences, and personally important events at school will be used as context variables to determine their associations with emotional distress and trauma symptoms. Participants receive a comprehensive explanation of the use of e-diaries as a spoken PowerPoint presentation and a written document in each participant’s respective language. After the presentation, the participant is asked to do a test trial on the smartphone. Smartphones are programmed with the e-diary app movisensXS^65^ and employ an hourly 1-week time-based e-diary design. Prompts are pseudorandomised within a time frame of 50–70 min to avoid expectancy effects. At the beginning of the study, participants are asked to enter their school schedules and determine their first prompt in the morning. On the weekends, e-diary assessments start at 10:00 hours no data are assessed during school hours. The prompts end at about 21:00 hours on school days and about 22:00 hours if there is no school the next day.

### Hair cortisol

If additional informed consent for hair cortisol collection is provided by study participants and their legal representatives, we collect thin hair strands from the posterior vertex of the head cut as close to the scalp as possible. Hair strands are tied together, sealed, and stored in a dry and dark place. Prior to analyses, they will be cut into a 2 cm segment proximal to the scalp, representing cumulative cortisol secretion of the last 2 months.^66^

### Quality assurance and monitoring

The study procedures are monitored by the Coordination Centre for Clinical Trials (KKS) Heidelberg according to the ICH-GCP^32^ with respect to a risk-based quality management strategy and ensure that the trial is conducted according to protocol and regulatory requirements. All data of the ongoing study are reviewed by an independent data monitoring committee once a year with special focus on safety issues.

Manual adherence across different therapists and participating centres is ensured by training all therapists on the START Adolescents programme and regular supervision with standardised assessments of manual adherence. We require a certain level of professional training from the therapists, of whom at least one per group must be a graduated psychologist, pedagogue, or physician.

The quality of psychometric assessments, tests and interviews is ensured by training the raters on the study assessments. Raters must have a bachelor’s or master’s degree in psychology or a comparable standard. Raters with a bachelor’s degree in psychology will administer questionnaires and psychological tests, raters with a Master‘s degree in psychology will administer the study interviews.

## Data management

The KKS Heidelberg is responsible for data management and analysis as well as data security and data transfer processes. All procedures are implemented in accordance with ICH-GCP guidelines and the Declaration of Helsinki.^32 67^ The protection of private data is ensured by a pseudonymisation procedure, and all private data are handled with respect to the European General Data Protection Regulation.^68^ Data are assessed by an electronic case report form (eCRF) and paper-based self-report questionnaires. The latter are transferred in copy to the KKS Heidelberg for double entry into the eCRF. E-diary data are transferred to the Mental mHealth lab, Karlsruhe Institute of Technology, analysed there and saved in encrypted form. The smartphones for e-diaries are provided by the research facility; no private smartphones are used for study purposes.

### Data availability

The research data generated during this study will be available on reasonable request by the study coordinating centre at the Department of Child and Adolescent Psychiatry, University Medical Center, Mainz, Germany. Anonymised data use by other researchers not involved in the study may be done with prior agreement.

## Statistics

### Sample size calculation

The sample size calculation is based on the coprimary outcomes of emotional distress (PSS-10) and traumatic symptoms (IES-R) at T1. Based on available studies^69 70^ we assume in our study an effect size of *d*=0.63 for the PSS-10 and of *d*=0.56 for the IES-R score at T1. This results in a required sample size of n=84 (PSS-10) and n=104 (IES-R) for a one-sided test at an *α*=0.025 level with a power of 80% to detect such differences. The START pilot trial showed a drop-out rate <10% and was conducted as a one-centre single-arm naturalistic trial with mostly inpatients.^20^ We, therefore, calculated the sample size on the assumption of 40% drop-outs between T0 and T1 to account for the multicentre, WL-controlled approach and unstable living conditions of the included population. This amounts to n=174 participants who need to be randomised in our trial.

### Analysis population and analysis

All randomised participants will be included in the full-analysis set as allocated. All randomised participants, who finish the study according to the study protocol until T2 as planned with no missing values for T1 (primary endpoint) will be included in the per-protocol set for analysis as allocated. All randomised participants will be included in the safety population according to the applied intervention.

Baseline characteristics will be analysed descriptively for the safety, full-analysis, and per-protocol set in the intervention and control group. The primary and coprimary endpoints will be analysed in the full-analysis set. Missing values will be imputed. Endpoints will be assessed as response variables in linear mixed regression models with site and psychotherapeutic group as random effects, intervention group, sex and region of origin as fixed effects, and age, PSS-10 and IES-R baseline scores, respectively, as linear effects with a hierarchical testing procedure that maintains the overall significance level of *α*=0.025. The primary analysis will be repeated in the per-protocol population as a sensitivity analysis. Since the different timing of the T0 baseline examination in the study groups after randomisation could cause biases in the effect estimates, that cannot be estimated or modelled, additional sensitivity analyses will be performed, such as repeating the primary analysis using the screening value instead of the baseline value. Secondary outcomes will be analysed in the full-analysis set. Missing values will not be imputed. The stability of treatment effects up to T3 will be assessed by calculating confidence intervals on the T1–T3 and T2–T3 difference for the PSS-10 and IES-R total scores in the intervention group. Psychometric scales used for assessment of secondary outcomes and hair cortisol concentrations will be analysed according to primary endpoints or descriptively. For the analysis of e-diary data, multilevel models will be used to characterise momentary mechanisms and context-dependent affective experiences, which allow a nested data structure (momentary experiences within participants), and enable different numbers of ratings per participant to be handled quite well.^71^ Safety variables will be analysed in the safety and full-analysis population.

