**Methods and analysis:**

This randomised, waiting-list-controlled, multicentre trial with a 12-week follow-up will include 174 refugee minors with partial or full post-traumatic stress disorder who are fluent in either Arabic, Dari, English, German or Somali. Eligible refugee minors will be randomised to the START or waiting-list control groups. The manualised 8-week START programme is based on techniques of dialectical behaviour therapy (DBT), fosters adaptive coping with emotional distress and traumatic symptoms and comprises eight therapy modules and a booster session. Study assessments are planned at baseline, post-treatment (ie, after programme participation or waiting time), booster session at week 12 or 12-week waiting time, and at the 12-week follow-up. Primary and coprimary outcomes are changes in psychological distress and traumatic symptoms at post-treatment and will be analysed as response variables in linear mixed regression models. Secondary outcomes are changes in further trauma-related and other psychopathological symptoms, emotion regulation and intermediate effects of the programme at follow-up. We will also assess effects of the programme with ecological momentary assessments and on neuroendocrine stress parameters using hair cortisol.

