### Trial design and setting

The study is conducted as a 12 weeks, two-arm, randomised, WL-controlled, multicentre trial with a 12-week follow-up and six participating outpatient departments in Germany, all of which are experienced in treating traumatised adolescent refugees. The study is coordinated by the Department of Child and Adolescent Psychiatry and Psychotherapy, University Medical Center, Johannes Gutenberg University, Mainz, Germany. The study intervention comprises an adapted version of the START programme.^18–20^ Languages used in the study for the intervention and the assessments are Arabic, Dari, English, German or Somali. Interpreters are involved if needed. The study is not blinded for the treatment condition, which will be evident to participants, caregivers and study therapists. Recruitment started 1 October 2020. We expect that the last participants will complete the study end of October 2022. Data base lock and analysis of primary outcomes are planned until end of December 2022.

Key stopping rules for patients are a withdrawal of informed consent, unwillingness to further participate in the trial, any factors affecting the patient’s or others’ well-being, for example, acute suicidality or acute endangerment to others, onset of other acute severe mental disorders, alcohol or substance abuse, inpatient treatment of over 2 days, start of concurrent psychotherapy and more than two psychotherapeutic crisis interventions. Key stopping rules for participating centres are non-adherence with the International Council for Harmonisation of Technical Requirements for Pharmaceuticals for Human Use: Guidelines for Good Clinical Practice (ICH-GCP)^32^ or the study protocol, insufficient recruitment of participants, or insufficient data quality. The key stopping rule of the trial is a change in the overall risk-benefit ratio.

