#### Baseline (T0), post-treatment (T1), booster session (T2), 12-week follow-up (T3) assessments

T0 takes place between one and 2 weeks after randomisation (WL) or before the first programme session (START), T1 within 1 week after the 8-week programme (START) or within 8–9 weeks after T0 (WL), T2 within 1 week after the booster session (START) or 4–5 weeks after T1 (WL) and T3 follow-up visits within 12 weeks after T2 (START/WL). At T0 only, the Post-Migration Living Difficulties Questionnaire (PMLD) and Questionnaire on Therapy Expectation are assessed. At the T0(T1)–T3 visits primary endpoints, trauma symptoms, emotion regulation, general psychopathology, overall clinical severity of mental disorders, suicidality and endangerment to others are assessed and 1 week e-diaries are applied. Hair cortisol is assessed at T0, T2 and T3. Adverse events are assessed at T0–T3 visits and weekly until T1.

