The original START Adolescents programme comprised five modules with psychoeducation on trauma, stress, distressing emotions and crises, mindfulness training, arousal regulation, stress reduction techniques, and handling nightmares. For the current study, the START manual^18–20^ was extended by the three additional modules 6–8 and a booster session. The additional modules provide an intensified training of stress reduction skills, mindfulness techniques and additional psychoeducation about emotions and interpersonal effectiveness. Each session follows a defined structure and comprises, as fixed repeated elements, mindfulness training, monitoring one’s own inner tension/stress (‘stress signal light’), reviewing experiences when applying the programme skills, new contents/psychoeducation and skills training. The final session in module 8 is dedicated to a farewell ceremony and to validating and rewarding the participants' efforts and achievements. During the booster session, which is scheduled 4 weeks after programme termination, participants review their experiences when applying the acquired skills and techniques, their open needs, and provide an outlook on their personal future wishes and goals. If standardised risk assessments or participants’ personal information reveal acute danger to the self or others, additional psychotherapeutic crisis interventions will be offered to the participant. Participants with ongoing acute suicidal tendencies or ongoing danger to others after two subsequent crisis interventions must be excluded from study participation and transferred to specific intense psychiatric care.

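### The per-protocol set requires conduct to T2, so the sensitivity analysis of the T1 endpoint drops participants for events after the outcome was measured

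*Protocol article*

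**What the plan says.** The Abstract of the protocol article fixes the time point of the primary outcomes: "Primary and coprimary outcomes are changes in psychological distress and traumatic symptoms at post-treatment". Post-treatment is T1, and the sample size calculation also refers to T1.

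The section on analysis population and analysis admits to the per-protocol set those randomised participants "who finish the study according to the study protocol until T2 as planned with no missing values for T1 (primary endpoint"). It gives this set a role in checking the main result: "The primary analysis will be repeated in the per-protocol population as a sensitivity analysis". The main result itself comes from a different set: "The primary and coprimary endpoints will be analysed in the full-analysis set. Missing values will be imputed".

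The section on the T0 to T3 assessments gives the timing. The first visit is "T1 within 1 week after the 8-week programme (START) or within 8–9 weeks after T0 (WL"), and the next is "T2 within 1 week after the booster session (START) or 4–5 weeks after T1 (WL"). The Intervention section places the booster: "During the booster session, which is scheduled 4 weeks after programme termination". The section on trial design and setting lists events that end a participant's trial participation, among them "inpatient treatment of over 2 days, start of concurrent psychotherapy and more than two psychotherapeutic crisis interventions". These rules are not tied to one arm.

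**The concern.** A per-protocol analysis of a T1 outcome asks what the contrast looks like among participants who followed the plan up to the moment the outcome was taken. The set as defined asks for more. A participant with a complete T1 assessment is removed if, in the following weeks, he or she withdraws, misses the booster or the T2 visit, or meets a stopping rule. None of these can change the T1 score or adherence to the 8-week programme. The reverse path is open: a poor T1 state can make someone stop attending, start other treatment or need crisis interventions.

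The condition also asks for slightly different things in the two arms. START participants have a booster session and a visit between T1 and T2; WL participants have the visit only.

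What is at stake is how the sensitivity analysis can be read. If it differs from the full-analysis-set result, a reader cannot separate the effect of non-adherence before T1 from selection after T1. If it agrees, the agreement says less than it should.

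**Working it through.** **1. Length of the extra interval.**
- START: T1 lies 0–1 week after programme end. The booster is 4 weeks after programme end and T2 is 0–1 week after the booster, so T2 is 4–5 weeks after programme end. The gap T1–T2 runs from 4 − 1 = 3 weeks to 5 − 0 = 5 weeks.
- WL: stated directly as 4–5 weeks.

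**2. Whom the T2 clause removes.** The set requires (a) protocol-conform completion to T2 and (b) no missing T1 values. Anyone lost before T1 already fails (b), and a deviation before T1 would still count under a rule that ended at T1. What the T2 clause adds is the removal of participants who are observed at T1 and followed the protocol up to T1.

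**3. The plan's own figures.** Inputs from the sample size section: d = 0.63 (PSS-10), d = 0.56 (IES-R), one-sided α = 0.025, power 80%, 40% drop-out between T0 and T1. Equal allocation is assumed. A two-sample t-test gives 82 for PSS-10 (plan: 84, an immaterial difference) and 104 for IES-R (plan: 104). Then 104 / (1 − 0.40) = 173.3, rounded up to 174, as stated. The drop-out allowance ends at T1, so nothing in it covers loss between T1 and T2.

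**4. Precision, illustration only.** The article gives no T1–T2 loss rate. Let x be an assumed further loss. The remaining number is 104 × (1 − x), and power is that of the t-test at d = 0.56 with half that number per arm.

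| Assumed T1–T2 loss | Remaining | Power (IES-R) |
|---|---|---|
| 0% | 104 | 0.81 |
| 5% | 98.8 | 0.79 |
| 10% | 93.6 | 0.76 |
| 20% | 83.2 | 0.71 |

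**5. Selection, illustration only.** If a fraction f of one arm's T1 completers leaves, and the leavers score g SD worse at T1 than the stayers, the mean of the stayers is better than the mean of the whole arm by f × g. With f = 0.15 and g = 0.5, both assumed, the shift is 0.15 × 0.5 = 0.075 SD, or 0.075 / 0.56 = 13% of the assumed IES-R effect. If the loss is in START and WL loses at random, the contrast moves towards START. If the selective loss is in WL, it moves by the same amount against START. If both arms lose similar participants at similar rates, the shifts largely cancel.

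**6. A second model of the same mechanism.** Suppose there is no true effect, one arm alone loses a fraction x, and the propensity to leave correlates ρ with a worse T1 score. The shift is ρ × φ(z) / (1 − x), where z is the (1 − x) quantile of the standard normal and φ its density. For ρ from 0.3 to 0.5 this gives about 0.03–0.05 SD at x = 5%, 0.06–0.10 SD at 10% and 0.10–0.17 SD at 20%. The sign again depends on which arm loses participants.

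**The case against.** The strongest defence is that the trial is described as a 12-week trial and the booster is session 17 of the programme, so completion to T2 can be taken to mean that the whole intervention was received. That is an intelligible definition, and it suits T2 and T3 outcomes. It does not carry over to T1, because the booster comes after the T1 assessment.

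Several further objections stand and limit the point.

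- The primary analysis uses all randomised participants as allocated, with imputation. The per-protocol set serves one sensitivity analysis and a baseline description, and no confirmatory decision rests on it.
- The arms differ less than it may seem. A reader might infer that WL participants need only wait, but they too must attend T2 and complete its assessments, and the stopping rules apply to both arms. The difference is one booster session.
- A reader might infer that the rule favours START. The article does not support a direction: distressed WL participants who start outside psychotherapy after T1 would also be removed, which would work against START.
- The shifts above are unadjusted. The planned model includes the baseline score, age, sex and region of origin, so any part of the gap explained by these would not bias the estimate.
- No power target is set for the per-protocol analysis. The figure of 104 is the planned number of T1 completers after an assumed 40% loss, not a per-protocol count under either definition.
- Every per-protocol set is selected after randomisation. Ending it at T1 removes only the T1–T2 part of that selection.

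A statistical analysis plan may give fuller per-protocol criteria. The point does not rest on missing detail, however, but on a rule that the article states.

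**Conclusion.** The point holds as a minor one. The stated rule conditions a check of the T1 result on conduct during the 3–5 weeks (START) or 4–5 weeks (WL) after T1, and the booster does not justify that for a T1 outcome. The sensitivity analysis is thereby open to avoidable bias of unknown sign and loses some precision.

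The size cannot be derived from the article. With assumed losses of 5–20%, IES-R power in the set falls from 0.81 to between 0.79 and 0.71. With assumed selective loss in one arm, the unadjusted contrast shifts by some hundredths of an SD up to about 0.17 SD, in either direction.

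It would go too far to conclude that the trial's primary result is compromised, or that the per-protocol result is worthless. The full-analysis-set result is untouched, and if few participants are lost between T1 and T2 the two definitions will give nearly the same set.

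**What to change.** For the sensitivity analysis of the T1 outcomes, define the per-protocol set by protocol adherence and data up to and including T1: programme adherence in START, or the waiting time to T1 in WL, with T1 values present. If a set complete to T2 is wanted, keep it as a separate set for T2 and T3 analyses only. Make the change before database lock.

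The cost is one changed sentence and possibly a second analysis set to program and report. No additional data or participants are needed, and the primary analysis does not change.

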#### Screening visit

Assessment of informed consent for study participation, inclusion and exclusion criteria, demographic and medical data. Inclusion of eligible participants, randomisation to the intervention (START) or WL using a web-based randomisation system with permuted blocks stratified by centre (http://randomizer.at).

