### Intervention

Details of the START Adolescents programme are provided in table 2. START Adolescents study groups comprise three to eight participants and are restricted to study participants, who have been randomised to the intervention group. The manualised START group programme is based on DBT-techniques with emphasis on coping with emotional distress and traumatic symptoms, resilience, adaptive functioning and self-efficacy, but not on confrontation with traumatic memories. The group therapy is provided by two therapists through twice-weekly 60 min sessions and interactions are based on validation and acceptance techniques. Written participant programme materials are available in all study languages and if necessary, translators will attend the group therapies.

**Table 2 T2:** Start adolescents programme, modules 1–8 and booster session

Before beginning of START: Written patient information. Handout. Every session: Mindfulness practice and stress signal light. Discussing between-session skills practice. Written patient material. Between the sessions: Participants are asked to train skills and techniques.		
	**Key interventions**	**Practice/training techniques**
**Module 1** Week 1 Sessions 1 and 2	Welcome. Introduction to START. Introduction of participants. Psychoeducation. Explanation of the concepts stress, high stress and stress-regulation skills. Teaching techniques. Skills for reducing distress and high distress. Relaxation techniques.	High-stress skills. Progressive muscle relaxation.
**Module 2** Week 2 Sessions 3 and 4	Consolidation: Available skills. Teaching techniques. Stress signal light for stress/inner tension monitoring and awareness. Emotion regulation strategies: mindful senses (hearing, feeling, tasting, watching, smelling). Skills box.	Mindful sensual experiences. Individual stress signal lights. Individual stimuli for distress/euthymia. High-stress skills. Individual skills boxes.
**Module 3** Week 3 Sessions 5 and 6	Consolidation. Individual skills boxes. Teaching techniques. Skills chains. Individual red light. Self-empowerment/resilience.	Skills chains Self-empowerment

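### The primary model adjusts for a T0 score taken after unblinded randomisation and on different clocks in the two arms, so the confirmatory estimate may be biased in either direction

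*Protocol article*

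**What the plan says.** All references are to the protocol article.

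- **Randomisation** is part of the screening visit: "Inclusion of eligible participants, randomisation to the intervention (START) or WL using a web-based randomisation system with permuted blocks stratified by centre" (Screening visit; Table 1 agrees).
- **T0** comes afterwards and is timed by a different rule in each arm: "T0 takes place between one and 2 weeks after randomisation (WL) or before the first programme session (START") (section on the T0 to T3 assessments). Table 1 gives 1 week for WL. The article states no maximum interval from randomisation to T0 in START; the 26-week limit under Trial flow runs from T0 to T3.
- **Groups** must be assembled first: "START Adolescents study groups comprise three to eight participants", all of them randomised to START (Intervention).
- **Blinding**: "The study is not blinded for the treatment condition, which will be evident to participants, caregivers and study therapists" (Trial design and setting).
- **Outcomes** are self-reported. The distress measure is the "Perceived Stress Scale, 10-item version (PSS-10), a validated self-report questionnaire", and the IES-R is also self-report (Primary endpoints).
- **Primary model**: the covariates include "age, PSS-10 and IES-R baseline scores, respectively, as linear effects" (Analysis population and analysis). Baseline here means T0, because the same section contrasts it with the screening value.
- **Acknowledged risk**: the section says that "the different timing of the T0 baseline examination in the study groups after randomisation could cause biases in the effect estimates", adds that such bias can be neither estimated nor modelled, and responds with sensitivity analyses, one of which substitutes the screening value.
- **Available alternative**: Table 1 schedules both PSS-10 and IES-R at screening.

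**The concern.** A baseline covariate is safe to adjust for when allocation cannot have affected it. T0 does not meet that condition: it is a self-report given by adolescents who already know whether they are about to start the programme or to wait. If that knowledge moves the T0 score, the adjustment carries part of the movement into the treatment effect.

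The clocks are a second, separate problem. If START participants wait for a group to fill while WL participants are assessed on a fixed schedule, T1 also falls at a different time since randomisation in the two arms. Natural recovery then differs between arms whichever covariate is used.

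The one-sided test at 0.025 on these two outcomes is the trial's confirmatory claim, and the T0-adjusted model is the one that carries it.

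**Working it through.** **1. The plan's own figures.** Two-sample t-test, one-sided 0.025, 80% power, 1:1 allocation (assumed; the ratio is not stated): d = 0.63 gives 41 per arm, 82 in total (plan: 84); d = 0.56 gives 52 per arm, 104 in total (plan: 104). With 40% drop-out, 104/0.6 = 173.3, which is 174 in whole pairs (plan: 174). The point does not rest on these figures, but the formula uses no baseline correlation, so changing the covariate leaves N at 174.

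**2. Bias from a shift at T0.** Let D0 and D1 be the START minus WL differences at T0 and T1 in SD units (lower is better), and rho the T0–T1 correlation. The adjusted effect is D1 − rho × D0. An arm shift of size s at T0 that has gone by T1 therefore biases the effect by rho × s. The documents give neither s nor rho, so both are assumed:

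| rho | s = 0.1 | s = 0.2 | s = 0.3 |
|---|---|---|---|
| 0.3 | 0.03 | 0.06 | 0.09 |
| 0.5 | 0.05 | 0.10 | 0.15 |
| 0.7 | 0.07 | 0.14 | 0.21 |

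This is 0.03/0.56 = 5% to 0.21/0.56 = 38% of the assumed IES-R effect. With s = 0 the bias is zero.

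**3. Direction.** If WL participants are disappointed or START participants hopeful, D0 is negative (START looks better at T0), −rho × D0 is positive, and the estimated benefit shrinks: bias against START. If the shift is reversed, the bias favours START.

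**4. Effect on the test**, with 104 evaluable, rho = 0.5 and s = 0.2. SE = sqrt(4 × (1 − 0.25)/104) = 0.170.
- Shift favouring START, no true effect: type I error = Phi(0.10/0.170 − 1.96) = 0.085 (0.079 in 5,000 simulated trials). Adjusting the same simulated data for a screening score gave a bias near 0 and an error of 0.023. Over the whole grid the error runs from 0.036 to 0.32.
- Shift against START, true effect 0.56: power = Phi(0.46/0.170 − 1.96) = 0.77, against 0.91 without the shift.

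**5. Possible START wait.** Last T3 at the end of October 2022 minus 24 to 26 weeks puts the end of accrual at about early May 2022, some 19 months after 1 October 2020. 174/6/19 = 1.53 randomised per centre per month, so about 0.76 to START. The mean wait to fill g places is (g − 1)/2/0.763 months: 5.7 weeks for g = 3 and 11.4 weeks for g = 5. This assumes uniform accrual, equal centres and groups that open when full. Against a WL midpoint of 1.5 weeks, the excess is 4.2 to 9.9 weeks.

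**6. Bias from unequal waiting.** Assume natural recovery of 0.02 SD per week, 8 extra weeks in START and rho = 0.6. START is then lower by 0.02 × 8 = 0.16 SD at both T0 and T1.
- T0 covariate: 0.16 − 0.6 × 0.16 = 0.064 SD in START's favour.
- Screening covariate: 0.16 SD in START's favour, since nothing offsets it.
- For 4.2 to 9.9 extra weeks: 0.034 to 0.079 SD (T0) and 0.084 to 0.198 SD (screening). With no recovery, or equal waits, both are zero.

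**7. Together.** At rho = 0.6, a disappointment shift of 0.2 SD gives 0.12 SD against START, and step 6 gives 0.064 SD for START: net 0.056 SD against. Other inputs reverse the sign.

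**The case against.** The plan has not overlooked the issue. It discloses it and pre-specifies at least one analysis with the screening value, so the dispute is partly about which of two planned models is primary. T0 is also a defensible choice on one ground: the T0–T1 window is about 8 weeks in both arms, so adjusting for T0 absorbs part of any unequal wait. Step 6 shows exactly that. T0 also does better if disappointment persists: a 0.2 SD shift present at both T0 and T1 leaves (1 − 0.6) × 0.2 = 0.08 SD after T0 adjustment and 0.20 SD after screening adjustment. All of this stands, and it is why replacing the covariate alone is no remedy.

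It does not make the present primary model safe. The screening-value analysis removes one source of bias and enlarges the other. If the two models disagree, the reader cannot tell which is closer to the truth; if they agree, opposing biases may be the reason.

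Three stronger readings are tempting but unsupported. A reader might infer that the result is certain to be biased, or biased towards START; the plan says only that bias could arise, and the most natural allocation effects work against START. A reader might infer that START's T0 and T1 always fall later; no minimum START interval is given, so someone joining a group about to open could be assessed earlier than a WL participant, and the full protocol may cap the wait. A reader might infer that participants lost before T0 drop out of the analysis; the plan keeps all randomised participants in the full-analysis set and imputes missing values.

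**Conclusion.** The point holds as a risk to the confirmatory estimate, not as a demonstrated bias. The order of events, the knowledge of allocation, the differing T0 rules and the use of T0 as covariate are all in the article. The sizes are not: 0.03 to 0.21 SD rests on assumed shifts of 0.1 to 0.3 SD that fade by T1 and correlations of 0.3 to 0.7; the 0.06 and 0.16 SD for unequal waiting rest on an assumed recovery of 0.02 SD per week, 8 extra weeks and a correlation of 0.6. The background section's remark that these problems often become chronic argues for slower recovery. The net direction is unknown. Neither the planned sensitivity analysis nor a covariate swap by itself resolves the problem. A reaction to allocation that lasts until T1 remains under any covariate in an unblinded waiting-list trial.

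**What to change.** Make two changes together.

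(a) In the primary model, use the screening PSS-10 or IES-R score as the baseline covariate, and move the T0-adjusted model to the sensitivity analysis. This takes a measurement that allocation can influence out of the confirmatory test.

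(b) For participants still to be randomised, schedule WL T0 and T1 from the start date of the START group opening at the same centre, so that time from randomisation to T0 and to T1 matches between arms. This removes the elapsed-time difference that (a) alone would leave more exposed.

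Report weeks from randomisation to T0 and to T1 by arm for everyone. This matters most for participants already randomised, for whom (b) comes too late and the unequal-waiting bias remains possible.

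Cost: (a) is a change of analysis wording, to be made before database lock; the screening score may explain slightly less variance. (b) needs a protocol amendment, and some WL participants will wait longer before T0. N stays at 174 and no visits are added. Randomising in batches once a group can be filled would also align the clocks, but it moves the wait ahead of randomisation for both arms; it is optional, not required.
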